## **4.4. Experimental procedure**

### 4.4.1. Selection of participants

Research participants who sign the informed consent form and answer to the health questionnaire (Appendices A and C) will receive an intraoral clinical examination to identify whether they meet the inclusion and exclusion criteria. All individuals will receive an assessment of their soft and hard oral tissues, findings will be recorded on the Hard and Soft Buccal Tissue Form (Appendix D). The initial questionnaire will be recorded on the Initial Examination Form (Appendix E). The first 150 individuals who meet the inclusion criteria, sign the consent form and the health questionnaire will be included in the study. After initial assessments, all individuals will receive a questionnaire to record daily symptoms associated with the flu and cold (Appendix F). This form will be delivered in physical format, with the questionnaire for the 90 days of the study, to facilitate completion by the participant. Once a week, participants must send photographs of their daily records. This will be sent via a messaging application. Participants will be reimbursed amounts compatible with internet packages. The research team undertakes to download the records and store them on devices on external physical drives, not connected to the internet. Messages will be deleted immediately after downloads. Furthermore, confidentiality of participants' data will be ensured throughout data storage and other procedures of this study.

The selection of participants will be of convenience based on a verbal invitation at the different clinics of the Dentistry Faculty of Federal University of Pelotas. In addition, recruitment may include posts on social media, which explain the main objectives of the present study. Those who express interest in participating in the study will receive the consent form in two copies and, after reading and signing it, will be evaluated based on the following exams:

4.4.2. Soft and hard oral tissue exams

All individuals will receive an examination of the soft and hard oral tissues. This exam will be performed by a single trained and calibrated examiner. With the aid of an odontoscope and artificial lighting from the dental chair, the examination will include an evaluation of the hard and soft palate, gingival mucosa, buccal mucosa, mucogingival areas, tongue, sublingual and submandibular areas, salivary glands and tonsillar, and pharyngeal areas. Findings will be recorded on the Soft and Hard Tissue Examination Form (Appendix D). If necessary, individuals will be immediately referred to the Stomatology Service of the Faculty of Dentistry at Federal University of Pelotas.

### 4.4.3. Allocation of participants in each group

Participants included will be randomly allocated to one of the two study groups, via a website (randomization.org). The examining dental surgeon and his assistant will not receive information, throughout the study, regarding the allocation group of each participant. The products will be covered by a wrapper to maintain allocation concealment. The products will be distributed by a researcher not involved in the clinical evaluations, in a separate area from the examination and interview site and placed in a sealed bag to avoid the perception of any differences in the packaging and appearance of the products used between the two experimental groups. Label information will consist of a study group code, instructions for home use, and safety information including emergency contacts (Appendix G).

Participants will be numbered, as a form of identification, chronologically from 001 to 150, as they are included in the study. Participants living in the same house will be assigned to the same experimental group, that is, they will receive the same products.

At the initial visit, as a form of guidance, participants will be instructed to practice oral hygiene according to the experimental regimen designated by a member of the research team. In the case of the control regime, participants will be asked to brush their teeth for 2 minutes with toothpaste twice a day. In the test regime, in addition to brushing for two minutes with toothpaste, participants must gargle with the substance offered for 30 seconds, twice a day.

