### 4.4.4 Home use products and instructions for use to the participants

Following the dental evaluation, all subjects will receive products according to the designated regimen for home use:

Control group: will receive a toothbrush with soft bristles for adults and a toothpaste. Instructions for use: brush your teeth for two minutes, twice a day (morning and evening) with the toothpaste provided.

Test group: will receive a toothbrush with soft bristles for adults, mouthwash and toothpaste. Instruction for use: brush your teeth for 2 minutes, twice a day (morning and evening) with the toothpaste provided. After brushing, gargle with mouthwash (20 ml) for 30 seconds, twice a day (morning and evening), and then spit it out.

Participants will be instructed to perform the procedures described above and only use the product assigned to their group during the study period. Products will be provided additionally on subsequent visits. There will be no restrictions on eating habits during the study, nor cleaning between teeth. Upon completion of the study, participants will be instructed to return all used products.

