## **4.7. Statistical analysis**

Chi-square test will be performed for gender data, and an independent t-test for the age variable, to test the hypothesis that the groups present balanced distribution of variables. The proportion of symptom-free days (i.e., none of the 10 symptoms were present) will be used for the primary outcome variable. Chi-square test will be used to compare the proportion of symptom-free days for the experimental groups. Analysis of variance can be used to compare groups. Significance level will be set at 95%.

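### Housemates are placed in the same arm, but no procedure for this is given, and the sample size and analysis make no allowance for household correlation

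*Combined protocol and SAP*

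**What the plan says.** Section 4.4.3 starts from individual allocation: "Participants included will be randomly allocated to one of the two study groups", through a website. Entry is sequential: "Participants will be numbered, as a form of identification, chronologically from 001 to 150, as they are included in the study". The same section then makes an exception for shared houses: "Participants living in the same house will be assigned to the same experimental group, that is, they will receive the same products".

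No section says how that exception operates. Allocation by household is not described. Housemates are not required to enrol together, entry is not limited to one person per house, and nothing is said about someone who joins after a housemate has been allocated. Recruitment (4.4.1) is open-ended: "The selection of participants will be of convenience based on a verbal invitation at the different clinics", with social media posts as a further route.

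Section 4.2.1 gives 60 individuals per group for 80% power and 75 per group after attrition, and mentions no household correlation. For the primary outcome, section 4.7 says: "Chi-square test will be used to compare the proportion of symptom-free days for the experimental groups". It allows analysis of variance as an alternative. Neither method is given a household term.

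On blinding, section 4.4.3 says: "The examining dental surgeon and his assistant will not receive information, throughout the study, regarding the allocation group of each participant". The participant can see the difference between arms. Section 4.4.4 states "Test group: will receive a toothbrush with soft bristles for adults, mouthwash and toothpaste", while the control group receives only a toothbrush and toothpaste.

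**The concern.** Two things follow from the same-arm rule.

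First, housemates who both take part do not receive independent allocations. Their outcomes are also likely to be correlated, since the symptoms counted are those of infections that spread at close quarters. When correlated people share an arm, an analysis that treats them as independent gives a standard error that is too small. The false-positive rate then exceeds its nominal level, and the power stated in 4.2.1 is somewhat optimistic.

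Second, if one member of a house enrols and another follows later, the second can learn the arm at home before deciding to join. People might come forward more readily when the first member was given the mouthwash, which would affect both the numbers and the case mix of the arms. A variance correction does not remove a bias of that kind. It has to be prevented by the order of consent and allocation.

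**Working it through.** **The plan's own figures.** The step from 60 to 75 per group reproduces as 60 × 1.25 = 75. The 60 cannot be reproduced, because 4.2.1 gives no effect size, event rate or standard deviation. I therefore take it as given that 60 independent, evaluable people per arm yield 80% power. Whether 25% attrition is better handled as 60 / 0.75 = 80 is a separate matter and is not used here.

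**Inputs from the documents.** 60 evaluable per arm and 80% power (4.2.1). The significance level is written as 95% in 4.7 and read as 0.05. The two-sided test is my assumption, as 4.7 does not state sidedness.

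**Inputs assumed.** f is the fraction of participants who live with one other participant, and ICC is the household correlation of a per-participant outcome. Neither is in the documents, so a range is shown.

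**Formulas.**
- Design effect for pairs: DE = 1 + f × ICC.
- Actual type I error when households are ignored: 2 × (1 − Φ(1.96/√DE)).
- Power when clustering is accounted for: Φ(2.802/√DE − 1.96), where 2.802 = 1.960 + 0.842 corresponds to 80% power under independence.

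| f in pairs | ICC | DE | Type I error, households ignored | Power, clustering accounted for |
|---|---|---|---|---|
| 10% | 0.2 | 1 + 0.10 × 0.2 = 1.02 | 5.2% | 79% |
| 20% | 0.2 | 1 + 0.20 × 0.2 = 1.04 | 5.5% | 78% |
| 30% | 0.3 | 1 + 0.30 × 0.3 = 1.09 | 6.0% | 76.5% |
| 40% | 0.5 | 1 + 0.40 × 0.5 = 1.20 | 7.4% | 72.5% |

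Worked for the last row: √1.20 = 1.095; 1.96/1.095 = 1.79, giving a two-sided error of 7.4%; 2.802/1.095 − 1.96 = 0.598, giving power 72.5%.

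The last two columns belong to different analyses and do not hold together. If households are ignored, the rejection rate under the planned effect is Φ(0.842/√DE), which is 79.8% at DE 1.02 and 77.9% at DE 1.20. That analysis keeps more apparent power only because it exceeds its nominal error rate.

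**In other terms.** The effective number per arm is 60/1.02 = 58.8 at the low end and 60/1.20 = 50 at the high end. A correct confidence interval is wider by a factor of √DE, about 1% and 10% respectively.

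**What the figures leave out.** They presuppose one outcome value per participant. A chi-square test on pooled days would also ignore repeated days within a person, which is a separate problem. They do not measure selective joining, for which the documents give no basis for a number.

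**The case against.** The strongest reply is that few housemates may enrol. Recruitment is by invitation in dental clinics and on social media, and nothing indicates that shared houses will be common. At f = 10% and ICC 0.2 the effect is hardly visible. That stands, and it limits the weight of this point. It does not remove the point, because the protocol provides for housemates and leaves their number open.

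Some stronger readings are tempting but not supported:
- A reader might infer that randomisation treats all 150 as independent. It does not: the household rule is an explicit exception within the allocation section. What is missing is a procedure for the exception and any allowance for it in 4.2.1 and 4.7.
- A reader might infer that allocation concealment fails outright. The risk arises only if housemates enrol at different times, and the documents do not say whether they will. Housemates who attend together could be allocated together.
- A reader might infer that enrolling staff also know the later housemate's arm. Sections 4.4.3 and 6.2 keep the examiner and assistant blind, the examining dentist signs the eligibility form (Appendix E), and products are handed out separately by someone outside the clinical evaluations. A housemate could disclose the arm, but that is a possibility and not what the plan describes. The supported risk is self-selection by the participant.
- A reader might infer from the visible forms that household membership is never recorded. Contact and consent material is not in the text reviewed, so this cannot be shown.
- A reader might choose harsher assumptions. Half of participants in households of three with ICC 0.5 would give DE = 1 + 0.5 × 2 × 0.5 = 1.50 and a type I error of 11.0%. Nothing in the documents motivates such a case.

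The same-arm rule itself may well be sensible, for example to prevent product sharing at home. This point does not argue against it.

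**Conclusion.** The omission is clear from the text: the plan allocates shared houses as units, gives no procedure for doing so, and carries none of it into the sample size or analysis. Whenever housemates with positively correlated outcomes enrol, the planned analysis understates the standard error.

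The size is uncertain. Over the assumed range of 10% to 40% of participants in pairs and ICC 0.2 to 0.5, the design effect runs from 1.02 to 1.20. Type I error is 5.2% to 7.4% if households are ignored, and power is 79% to about 72% if clustering is accounted for. This rests on 60 independent people per arm giving 80% power, a two-sided 0.05 test and a per-participant outcome. The effect could be negligible or moderate, and the documents do not settle which. Selective joining is conditional on staggered enrolment and cannot be sized. The plan should be changed, because household links and consent before allocation are hard or impossible to restore afterwards, but this point alone does not undermine the trial.

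**What to change.** Keep the same-arm rule and make these changes:
- **Identifier.** Record a household identifier for every participant at screening.
- **Section 4.4.3.** Allocate each household once, after all its interested members have consented and completed baseline. A person with no participating housemate is a household of one. A member who joins later goes into the household's arm, is flagged, and is left out in a sensitivity analysis.
- **Section 4.7.** Analyse one outcome per participant with household-clustered standard errors, counting single-person households as clusters of one. The number of clusters stays ample. With 120 evaluable participants and 40% in pairs there are 72 singles and 48/2 = 24 pairs, so 96 clusters.
- **Section 4.2.1.** State that the 80% power assumes independent participants, and give the power under an assumed design effect (for example 76.5% at 1.09). N need not be raised.

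The cost is one recorded item, short additions to three sections, a slightly wider confidence interval, a somewhat lower stated power, and a short wait before shared households are allocated.

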### 4.4.4 Home use products and instructions for use to the participants

Following the dental evaluation, all subjects will receive products according to the designated regimen for home use:

Control group: will receive a toothbrush with soft bristles for adults and a toothpaste. Instructions for use: brush your teeth for two minutes, twice a day (morning and evening) with the toothpaste provided.

Test group: will receive a toothbrush with soft bristles for adults, mouthwash and toothpaste. Instruction for use: brush your teeth for 2 minutes, twice a day (morning and evening) with the toothpaste provided. After brushing, gargle with mouthwash (20 ml) for 30 seconds, twice a day (morning and evening), and then spit it out.

Participants will be instructed to perform the procedures described above and only use the product assigned to their group during the study period. Products will be provided additionally on subsequent visits. There will be no restrictions on eating habits during the study, nor cleaning between teeth. Upon completion of the study, participants will be instructed to return all used products.

### 4.4.5 Subsequent assessment

Subsequent evaluations will be performed after 30 and 90 days of use of the designated products. Participants will attend the research location to be evaluated and receive additional products, according to the group to which they were allocated. During these visits, an Oral Assessment of Soft and Hard Tissues will be carried out (Appendix D). A Visit Form (Appendix H) will be completed for all study participants.

After the 90 days of the experiment, all participants will be instructed to no longer use the products provided, returning to their normal oral hygiene habits. All unused products will be handed over to an assistant not involved in the clinical examination and will be discarded following Federal University of Pelotas waste disposal guidelines.

- 1. **Monitoring and discontinuity of participants**

All randomized research participants who receive the products will be monitored according to the following protocol:

Participants will be considered to have completed the study if they are re-evaluated at the end of 90 days. They will only be considered lost to follow-up if no contact was established during the completion of the study, and there is, therefore, insufficient information to determine the status of the research participant. Efforts will be made to determine the reasons why the participant did not return for the required visit(s) or the reasons for the participant's withdrawal from the study. Participants will exit the study if any of the following occur:

1. Participant who substantially fails to follow the required protocols;

2. Participant who fails to attend scheduled appointments;

3. Participant who is treated, during the study period, with medications that may interfere with the study parameters being analyzed;

4. Participant who is treated by a medical or dental service, and this may interfere with the parameters being analyzed in the study;

5. Participant who develops serious adverse reactions. The investigator will immediately record the information on the Adverse Reactions Form (Appendix B);

6. The participant who chooses to end their participation in the study;

7. Participant reports being pregnant during the study.

The researcher will be responsible for promptly notifying the Federal University of Pelotas Research Ethics Committee about all participants who leave the study prematurely and experience serious adverse effects.

## **Pregnancy**

There is no intention to include pregnant women in the present study. If any woman becomes pregnant during this clinical study, her participation will be terminated and there will be a notification of the event by the responsible researcher.

## **4.7. Statistical analysis**

Chi-square test will be performed for gender data, and an independent t-test for the age variable, to test the hypothesis that the groups present balanced distribution of variables. The proportion of symptom-free days (i.e., none of the 10 symptoms were present) will be used for the primary outcome variable. Chi-square test will be used to compare the proportion of symptom-free days for the experimental groups. Analysis of variance can be used to compare groups. Significance level will be set at 95%.

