**If yes, explain: _________________________________________________**

**Are you doing any medical treatment?** ( ) Yes ( ) No

If yes, explain: __________________________________________________

**This year (2022), have you been vaccinated against common flu (Influenza)?** ( ) Yes ( ) No

Have you been vaccinated against **SARS-CoV-2 (Covid-19)?** ( ) Yes ( ) No

Have you ever been treated or diagnosed with any of these conditions?

( ) Abnormal bleeding

( ) Hemophilia

( ) Blood transfusion

( ) Ulcer/Colitis

( ) Heart problems

( ) Epilepsy/fainting

( ) Asthma

( ) Arthritis

( ) Glaucoma

( ) Drug abuse

( ) Skin problems

( ) Blood diseases

( ) Chemotherapy/Radiotherapy

( ) Diabetes/Abnormal blood sugar

( ) Breathing difficulties

( ) Lung problems

( ) High or low blood pressure

( ) Anemia

( ) AIDS

( ) Cancer/Tumor

( ) Kidney or liver disease

( ) Hepatitis/Jaundice

( ) Emphysema

( ) Rheumatic fever

Please, describe the conditions cited above: __________________________________________________________________________________________________________________________________________________________________________________________________________________

Height:______ Weight: _______ Blood pressure: _________

Are you allergic to any oral care product, personal hygiene product, or any of its ingredients? ( ) Yes ( ) No

If there is, explain: ____________________________________

Do you use any medication daily?

| **Name of the medication** | **Dose** | **Daily frequency** | **Reason** |
| --- | --- | --- | --- |
|  |  |  |  |
|  |  |  |  |
|  |  |  |  |
|  |  |  |  |
|  |  |  |  |

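### Baseline data serve only balance tests on gender and age; the primary comparison is unadjusted and no symptom score is taken before allocation, so some precision may be lost

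*Combined protocol and SAP*

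**What the plan says.** Section 4.7 (Statistical analysis) tests gender by chi-square and age by t-test, "to test the hypothesis that the groups present balanced distribution of variables". It does not say what follows from either result.

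On the outcome, the same section states: "The proportion of symptom-free days (i.e., none of the 10 symptoms were present) will be used for the primary outcome variable". The comparison is: "Chi-square test will be used to compare the proportion of symptom-free days for the experimental groups". It adds: "Analysis of variance can be used to compare groups". No covariate is named for either method. Section 4.4.3 names no stratification factor for the randomisation and places participants from one household in the same group.

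The initial visit already yields more. Appendix C asks for date of birth, smoking (yes, no, ex-smoker) and vaccination against influenza and COVID-19. It has tick boxes for asthma, emphysema, lung problems and "Breathing difficulties". Appendix E also records age. Of these, section 4.7 uses only age, and only in a balance test.

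On timing, section 4.4.1 says: "After initial assessments, all individuals will receive a questionnaire to record daily symptoms associated with the flu and cold (Appendix F". Section 5.3 does not list Appendix F among the initial-visit forms. The eligibility lists in section 4.2 and Appendix E have no explicit item on a current cold or chronic nasal symptoms. They do require good general health as judged by the investigators.

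**The concern.** A balance test after randomisation asks whether chance produced the difference between groups. If allocation was sound, the answer is already known. A non-significant result does not show that the groups are alike on what matters, and a significant one leads nowhere because no action is attached.

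What protects the comparison against chance imbalance is prespecified adjustment for variables that predict the outcome. The plan has none, either through stratification or in the analysis.

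The outcome makes baseline symptoms especially relevant. A day counts as symptom-free only if all ten Appendix F symptoms are absent, and these include stuffy nose, sneezing and tiredness. A participant with a permanently stuffy nose would score 0 of 90 days whatever the product does. Such people add between-person variance in both arms, and without a pre-allocation score the analysis cannot account for it.

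At stake are the width of the interval and the credibility of any adjustment made later, which would be post hoc if no list is fixed now.

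**Working it through.** **The plan's own figure.** The plan states no figure for precision or for variance explained. Its 60 per group for 80% power cannot be reproduced, because no effect size, standard deviation or event rate is given. The sample-size text does give the likely analysis set: 75 per group with 25% attrition leaves 75 × 0.75 = 56.25, or about 56 per group and N = 112.

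**What the balance tests can do.** With two independent tests at 5% and true nulls, the chance of at least one false signal is 1 − 0.95² = 9.75%. At 75 per group, the power to flag a binary covariate is 23% for 50% v 60% and 46% for 50% v 65%. The tests therefore miss sizeable imbalance. These figures treat participants as independent.

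**A non-significant imbalance can still matter.** Let the covariate imbalance be z = 1.5 (p about 0.13) and let the covariate explain R² of the outcome variance. Given that imbalance, the unadjusted statistic has mean 1.5·√R² and standard deviation √(1 − R²). The chance that it exceeds 1.96 in absolute value is:
- R² = 0.10: mean 0.474, SD 0.949, giving 6.4%
- R² = 0.20: mean 0.671, SD 0.894, giving 7.6%

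Averaged over all randomisations, the rate remains 5%.

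**Gain from adjustment, before its cost.** For a continuous participant-level outcome, the standard error ratio is √(1 − R²).

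**Cost.** Estimating p covariate coefficients multiplies the variance by about 1 + p/(N − p − 3). With N = 112 and p = 5 this is 1 + 5/104 = 1.048. The net ratio is √[(1 − R²) × 1.048].

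| Assumed R² | SE ratio before cost | Change | Net SE ratio, p = 5 | Net change |
|---|---|---|---|---|
| 2% | 0.990 | −1.0% | 1.013 | +1.3% |
| 5% | 0.975 | −2.5% | 0.998 | −0.2% |
| 10% | 0.949 | −5.1% | 0.971 | −2.9% |
| 20% | 0.894 | −10.6% | 0.916 | −8.4% |

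**Break-even.** Setting the net ratio to 1 gives R² = p/(N − 3):
- p = 5: 5/109 = 4.6%
- p = 7: 7/109 = 6.4%
- p = 11: 11/109 = 10.1%

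A long list reaches 11 quickly: age 1, sex 1, vaccination 1, three-level smoking 2, respiratory history 1, enrolment month up to 4 (the schedule allows five months for selection and data collection), baseline score 1. The list should therefore be short.

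**The case against.** The strongest reply is that nothing here invalidates the trial. Chance imbalance does not bias a randomised comparison, a valid unadjusted interval already allows for it, and deleting tests with no stated consequence changes no conclusion. That stands. A reader might infer that the primary result would be biased by unadjusted covariates or by colds present at entry. The documents do not support this: such symptoms are expected equally in both arms.

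A reader might also carry the plan's 80% power forward, get about 77% at 56 per group, and claim that adjustment lifts it to 82–90%. That does not hold as a result for this trial. The sample-size text states power for the occurrence of flu-like symptoms, not for symptom-free days. The factor √(1 − R²) belongs to a continuous outcome. An R² of 10–30% has no source in the documents, and the calculation ignores the cost in degrees of freedom. In a population selected for good health, R² could be lower.

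Three further points are fair:
- Screening for symptoms at entry is not wholly absent. Investigators judge general health, the examination covers the tonsillar and pharyngeal areas, and section 7 lets the investigator turn away users of products that could obscure the results. These screens are partial and discretionary, and none produces a baseline score.
- The null of a balance test is not quite true by design for individuals, because later household members follow the first. That does not rescue the tests, which also assume independent participants.
- Baseline symptom burden, plausibly the strongest predictor, is not collected. The data already in hand may therefore be worth little, and much of any gain would need the extra page.

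**Conclusion.** The point holds as a modest efficiency and good-practice recommendation. Section 4.7 spends its only use of baseline data on tests that cannot inform the comparison. It leaves smoking, influenza vaccination and respiratory history unused, and no symptom score precedes allocation.

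The benefit of changing this is precision and protection against chance imbalance, not removal of bias. Its size depends on R², which the documents do not give. With five covariates and about 56 per group, the net change in standard error runs from about 1% worse at R² = 2% to about 8% better at R² = 20%, with break-even near 5%. This assumes a continuous participant-level outcome, independent participants and linear covariate effects. Household clustering would alter the figures somewhat.

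The point also depends on a prior change: a chi-square test cannot take covariates, so adjustment is possible only once the participant becomes the unit of analysis.

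**What to change.** 1. Delete the balance tests in section 4.7 and present a table of baseline characteristics by group, including gender, without p-values.
2. Have each participant complete one Appendix F page at the initial visit before allocation, and add it to the initial-visit forms in section 5.3. The symptom items cover the previous 24 hours, so the score would describe the period before product use.
3. Replace the chi-square test and the optional analysis of variance with one prespecified model of each participant's proportion of symptom-free days, for example linear or quasi-binomial, with robust standard errors clustered by household.
4. Fix the covariates in advance: baseline symptom score, age, influenza vaccination, current smoking (yes/no), and any asthma, lung or breathing condition (yes/no). Report the unadjusted estimate beside the adjusted one.

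The cost is SAP wording, one diary page at a visit that already takes place, and about 5 degrees of freedom. If these covariates explain less than about 5% of the variance, there is little or no net gain in precision and possibly a very small loss.
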